**12.2.1 Implementation evaluation**

We will use a previously described approach informed by the Consolidated Framework for Implementation Research (CFIR) (35). We will collate data from focus groups, questionnaires as well as field notes of clinicians, taken by the ReNs documenting feedback at the time of the intervention implementation. The transcribed interviews and field notes will be analysed using a deductive qualitative content analysis technique recommended for CFIR. The analysis will be performed by two researchers independently using the CFIR NVivo template pre-populated with construct codes – NVivo is a qualitative data analysis computer software package produced by QSR International [QSR International Pty Ltd. (2020) NVivo (released in March 2020) [https://www.qsrinternational.com/nvivo-qualitative-data-analysis-software/home](https://www.qsrinternational.com/nvivo-qualitative-data-analysis-software/home?_ga=2.227843295.371367470.1635126007-457000355.1635126007)]. The outputs of the analysis will be actionable recommendations to optimise the pathway and improve implementation.

**12.2.2 Cost effective analysis**

## We will record data, analyse, and report cost-effectiveness findings following guidelines for trial-based cost-effectiveness analyses (50), including reporting resource use and costs (healthcare perspective) for each trial condition. Healthcare utilisation data will be costed using actual costs (e.g., device costings) when available or market rates. Intervention provision costs to deliver usual care or INPREP during the trial (12-month time-horizon for patients) will be recorded and applied at a per-patient level. A trial-based incremental cost-effectiveness ratio (ICER) will be estimated for the incremental cost per additional patient successfully completing NPWT. ICER=[(CostNPWT) minus (Costusual care)] / [(EffectNPWT minus Effectusual care)]. Due to the potential for uncertainty and non-normal distributions, 95%CIs (for costs and effect estimates) and a 95% confidence ellipse (for ICER) will be derived from bootstrap resampling. In addition, Markov modelling (5-year time-horizon) will be used to extend these cost-effectiveness findings by generating estimates for the consequences (on costs and patient outcomes listed above) of implementing INPREP at all specialist paediatric hospitals in Australia using data from this trial and prior studies as well as health service and population profile data (e.g. Australian Bureau of Statistics). In addition to probabilistic sensitivity analyses, we will assess sensitivity of results to variation in measured resource use, unit costs, effectiveness, time-horizon, and discounting (one way and multi-way sensitivity analyses).

**13. ETHICAL CONSIDERATIONS**

Central ethical approval will be obtained from Children’s Health Queensland (CHQ) HREC via Ethics Review Manager with accompanying Victorian Specific Module (VSM) and Western Australian Specific Module (WASM). Expedited affiliated academic institution ethics approval will be sought from (Griffith University, University of NSW, Queensland University of Technology, University of Western Australia, and Monash Children’s Research Institute). A site-specific agreement (governance) will also be obtained for QCH. This is a national multi-centre investigation employing a hybrid type III effectiveness-implementation design. Four major Australian paediatric burn centres are participating:

- The Children’s Hospital at Westmead (CHW)
- Perth Children’s Hospital (PCH)
- Queensland Children’s Hospital (QCH)
- Royal Children’s Hospital Melbourne (RCHM)

The QCH is the lead site for this multi-centre investigation. Initial HREC approval will be sort by the lead site, and subsequently shared with the other three sites (The Children’s Hospital at Westmead, Royal Children’s Hospital Melbourne, and Perth Children’s Hospital). Each site will then be responsible for submitting local Governance and site-specific agreements. This study will be performed in accordance with the ethical principles of the Declaration of Helsinki, ICH GCP for Guidance on Good Clinical Practice and National Health and Medical Research Council (NHMRC) National Statement on Ethical Conduct in Research Involving Humans (NHMRC, Australian Research Council, and Australian Vice-Chancellors' Committee, 2007; World Medical Association, 2008) (51-53). No part of the study will commence prior to notifying CHQ HREC and governance.

**13.1 Safety considerations/Patient safety**

In accordance with ICH Good Clinical Practice guidelines and national regulations, all adverse events (including those not directly related to the child’s burn) will be recorded and submitted to the appropriate HREC and governing bodies. An adverse event (AE) is defined as any untoward, unfavourable, or unintended medical occurrence in a patient administered an investigational product – which does not necessarily have a causal relationship with the medicinal investigational product. Research and data collection methods outlined in this protocol have been included in previous studies at QCH with no adverse events. Although AE are not anticipated, [name] [name] who is a practicing child psychologist with extensive experience with this population in this environment will be involved in the co-design process to minimise any potential distressing triggers for patients and/or their parents/carers. There will also be resources available for families to access throughout the study, including the burns social worker or referral to lifeline etc. The investigators at each partnering hospital will be responsible for recording all adverse events – regardless of their causal attribution to the burn NPWT intervention, with the following exceptions:

- Conditions and comorbidities that are present at initial screening following patient presentation and do not deteriorate will not be considered adverse events
- Abnormal laboratory values (from biospecimen samples) will not be considered adverse events unless deemed clinically significant by the site investigator

Investigators at each site will obtain information on AEs at each patient contact, and all AEs will be recorded in the patient’s medical records. Adverse Events Grade 2 or higher will be reported to the lead HREC and sponsor immediately, as per reporting requirements (see Table 1 below for AE grade definitions).

Table 1. Adverse Event Grading Scale

| **AE Grade** | **Severity** | **Unique Clinical Descriptors** |
| --- | --- | --- |
| Grade 1 | Mild | Asymptomatic or mild symptoms; clinical or diagnostic observations only; intervention not indicated |
| Grade 2 | Moderate | Minimal, local or non-invasive intervention indicated; limiting age-appropriate instrumental activities of daily living |
| Grade 3 | Severe or medically significant but not immediately life-threatening | Hospitalisation or prolongation of hospitalisation indicated; disabling; limiting self-care activities of daily living |
| Grade 4 | Life-threatening consequences | Urgent intervention indicated |
| Grade 5 | Death related to AE | Death |

*Adverse event terminology and descriptors presented above in Table 1 were taken from Version 5 of the *Common Terminology Criteria for Adverse Events,* US Department of Health and Human Services, National Cancer Institute (2017).

<https://ctep.cancer.gov/protocoldevelopment/electronic_applications/docs/ctcae_v5_quick_reference_8.5x11.pdf>

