***Secondary Patient Outcomes:***

1. *Healing outcomes:* i) Time/days to re-epithelialisation (blinded photo assessment), ii) skin grafting requirements, iii) burn wound exudate, iv) number of dressing changes, v) adverse events (26).
2. *Operating theatre requirements:* i) proportion patients requiring an operation (%), ii) operations required per patient, iii) operative procedures performed (e.g., skin graft) (26).
3. *Hospital requirements 12 months post-injury:* i) proportion of patients needing ≥1 admissions to hospital (% & length of stay), ii) number of outpatient appointments, iii) number of scar clinic appointments.
4. *NPWT device malfunctions:* i) alarms ii) charging issues

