**8.4 STUDY PROCEDURES**

Five steps will be sequentially rolled out across the 4 hospitals over 13 months: **1. Set up** ensures adequate training and collection of control and intervention data. **2. Control steps**-are usual care, i.e., standard silver dressings. **3.** **Intervention establishment** involves the research nurses (ReNs) collaborating with the NAG and local champions to promote the INPREP Pathway and delivering the companion implementation strategies. A project manager will develop a study manual and training schedule for ReNs, monitor data integrity, intervention fidelity log and collaborate with the team (ReNs and CIs) to promote intervention fidelity. **4. Implementation period** is intervention exposure. **5. Sustainability** of adherence measured. In both control and implementation steps other burn care will be as per local standards (40). Implementation education will provide evidence-based advice, but treating clinicians will determine definitive care (e.g., inpatient versus outpatient care) based on patient needs and healthcare priorities.

**Figure 2.** Steps for the multi-centre, prospective, pragmatic, stepped-wedged randomised controlled trial

[figure not shown]

**Figure 2**. Illustrates the five steps of the multi-centre, prospective, pragmatic, stepped-wedged randomised controlled trial that will be conducted across the four participating paediatric hospitals. Following initial set up, all participating sites will start the trial in control phase with the baseline measures taken, and then one site will randomly step up (computer-generated, centralised randomisation) to implementation every 6 weeks, until saturation of the implementation intervention across all sites.

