**12. STATISTICAL CONSIDERATIONS AND DATA ANALYSIS**

**12.1 Sample size and statistical power**

Our project follows a pragmatic design to best allow the NPWT Pathway intervention to be tailored to the site context. The study will be conducted across four state’s tertiary paediatric burns centres. All sites will start the trial in control phase with the baseline measures taken, then one site will randomly be allocated (i.e., NPWT implemented across the site) (using computer-generated, centralised randomisation) to implementation every 6 weeks, until the new intervention has been implemented across all sites at 13 months. At 13 months after implementation has occurred across all sites, adherence sustainability will be measured to inform implementation effectiveness. Using a step wedge study design, and four sites with a minimum of 100 individuals recruited from each site (recruiting patients until the capacity of the site is reached), we would be able to detect a difference of 10% in adherence rate with 94% power (5% alpha). We expect an improvement of 10% in adherence from 10% in controls to 20% in the treatment. A greater difference in adherence, with the same parameters otherwise, will result in higher power and thus the above is the minimum numbers expected. Calculations were performed with the shiny app from Hemming et al. (2015) (38). We anticipate a minimum of 120 potential patients per site, which will be more than the above estimate and thus the power of this study is expected to be >94%.

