**12.2 Statistical analysis methods**

Generalised Linear Mixed Models (fitting a random intercept to account for clustering, random effect) and Generalised Estimating Equations (using the individual as the clustering unit) will be used to compare the effect of switching from the usual care to INPREP condition on primary and secondary outcomes. Specifically, an appropriate protocol for model selection based on Zuur *et al*. (2009) will be applied (49). This analysis approach is able to account for potential temporal trends, using time as a covariate, in addition to clinical explanatory variables (total body surface area, age, gender), which will be included in each model. It should be noted that other covariates, such as time, could be used as random effects in the mixed models.

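### Section 13.1 defines an adverse event only in patients given an undefined investigational product, which conflicts with its own recording rules and with the planned comparison of adverse events

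*Protocol*

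**What the plan says.** **Definition (Protocol 13.1).** An adverse event is "any untoward, unfavourable, or unintended medical occurrence in a patient administered an investigational product". The sentence adds that a causal link to the *medicinal investigational product* is not required. Neither term is defined anywhere in the protocol.

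**Recording rules (Protocol 13.1).** The same section says that "all adverse events (including those not directly related to the child’s burn) will be recorded", and makes site investigators responsible for recording events "regardless of their causal attribution to the burn NPWT intervention". Information is to be sought whenever the patient is seen. Only two exceptions are listed: pre-existing conditions that do not worsen, and laboratory abnormalities that are not clinically significant. The healing outcomes text under the measurement tools also says that adverse events will be documented, without limiting this to NPWT recipients.

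**Outcome and analysis.** The Secondary Patient Outcomes in 8.3.2 include "iv) number of dressing changes, v) adverse events (26" (the trailing number is a literature reference). Section 12.2 says the models will "compare the effect of switching from the usual care to INPREP condition on primary and secondary outcomes".

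**Conditions.** Under 8.4 the control steps "are usual care, i.e., standard silver dressings". On uptake, 12.1 states: "We expect an improvement of 10% in adherence from 10% in controls to 20% in the treatment".

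**The concern.** The definition fits a trial in which every participant receives a study product. Here a large share of children receive silver dressings alone. On the ordinary reading such a child has not been given an investigational product, so an infection in that child would not meet the definition, while the same infection in a child on NPWT would.

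The dividing line is receipt of NPWT, not trial period. Control-period children on silver dressings fall outside, and so do implementation-period children who do not receive NPWT. Any control-period child who does receive it falls inside.

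Adverse events are an outcome to be compared between conditions. If a site follows the definition literally, the chance that an event is counted rises with NPWT uptake, and uptake is what the intervention is meant to raise. Any excess under INPREP could then come from the counting rule, and no background rate in silver-only children would be available to judge it. The immediate reporting of Grade 2 or higher events in 13.1 uses the same term and would inherit the same limit at such a site.

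**Working it through.** The protocol states no figure for adverse events, so there is nothing to reproduce. The check is mainly a comparison of texts, followed by an illustration.

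**Step 1: do the passages agree?**

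| Place | What it covers |
|---|---|
| 13.1, definition | Only patients given an investigational product; causality not required |
| 13.1, recording rules | All adverse events, whatever the attribution, with two unrelated exceptions |
| Healing outcomes text | Adverse events documented, no limit by condition |
| 8.3.2 with 12.2 | Adverse events are a secondary outcome, compared between usual care and INPREP |
| Appendix 5, schedule | No adverse event row, so no tie-break |

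The clause "regardless of their causal attribution to the burn NPWT intervention" waives the test of causality. It does not waive the test of exposure in the definition. The recording rules carry no exposure limit of their own, but they use the term that the definition restricts. No sentence says that children without NPWT are covered, and none says that they are excluded. Two sites could follow the protocol and record differently.

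**Step 2: what would a literal reading do?**

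Let r be the true adverse event risk, equal in both conditions, and let u be the share of children given NPWT. If an event counts only in a child given NPWT:

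- counted rate = u × r
- spurious ratio = (u in implementation × r) / (u in control × r) = u in implementation / u in control

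Inputs: u = 0.10 and 0.20. These are the *adherence* figures in 12.1, used as a proxy for receipt. Section 8.3.1 defines adherence by eligibility and duration of application, so receipt may differ. The values of r are assumptions.

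| r (assumed) | Control counted | Implementation counted | Ratio |
|---|---|---|---|
| 5% | 0.10 × 5% = 0.5% | 0.20 × 5% = 1% | 2.0 |
| 10% | 0.10 × 10% = 1% | 0.20 × 10% = 2% | 2.0 |
| 20% | 0.10 × 20% = 2% | 0.20 × 20% = 4% | 2.0 |

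The ratio does not depend on r, but it does depend on receipt. With control receipt kept at 10% and implementation receipt assumed to be 50% or 90%, it is 0.50/0.10 = 5 or 0.90/0.10 = 9. If no control child received NPWT, no control event could be counted.

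**Step 3: what if the recording rules prevail?**

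Every enrolled child counts, the counted rate is r in both conditions, and the ratio is r/r = 1.0.

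**Step 4: what if only some sites read it literally?**

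Suppose one of the four sites does, with equal numbers per site in each condition (an assumption). The counted rate in control is (0.75 + 0.25 × 0.10) × r = 0.775r, and in implementation (0.75 + 0.25 × 0.20) × r = 0.80r. The crude ratio is 0.80/0.775 = 1.03. The bias is therefore large only if the literal reading is widespread.

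**The case against.** The strongest reply is that the working instructions are not restricted. Section 13.1 opens by saying that all adverse events are recorded, has sites ask about them throughout, and gives a short list of exceptions that does not name usual-care children. The healing outcomes text lists adverse events beside grafts and scar referrals, which plainly apply to everyone. Where the protocol does limit collection by condition it says so: footnotes 5 and 7 of Appendix 5 confine implementation outcomes and first-dressing-change wound fluid to the intervention arm. Nothing similar is said of adverse events. In addition, 8.3.2 cites an earlier NPWT trial beside adverse events rather than section 13.1, and since the product is undefined, a site might read the term broadly.

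Most of this stands, and it limits what can be claimed. A reader might infer that the adverse event comparison is already distorted, that the control count will be nearly empty, or that safety reporting is confined to children on NPWT. The documents do not support any of these. They show conflicting text, not how sites will resolve it. Nor do they support presenting the ratio of 2.0 as an expected bias, because it needs a literal reading at every site and adherence standing in for receipt.

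The reply does not remove the conflict. An instruction to record all adverse events still relies on the only definition given, and the schedule of assessments has no adverse event row to settle the matter. This is also not a detail that can be assumed to sit in a statistical analysis plan: the protocol itself states the definition, and states it in a way that does not fit the design.

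**Conclusion.** The definition in 13.1 does not suit a stepped-wedge trial with a usual-care condition. It contradicts the unrestricted recording rules around it and the between-condition comparison in 12.2. The consequence is conditional. If sites apply the definition as written, ascertainment depends on NPWT receipt and, where receipt is higher under INPREP, the comparison is biased towards more events under INPREP. If the recording rules are applied to every enrolled child, there is no distortion.

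At 10% and 20% receipt the spurious ratio runs from 1.0 (no site reads it literally) to 2.0 (every site does). The upper end is a worst case as to how the definition is applied. It assumes equal true risk and adherence as a proxy for receipt, and a wider gap in receipt would raise it. The sample size and power statements are not affected.

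**What to change.** In 13.1, make three changes:

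1. Define an adverse event as any untoward medical occurrence in any enrolled child, in any trial period and whether or not NPWT was applied.
2. Delete the reference to a medicinal investigational product.
3. State that adverse events are ascertained in the same way in the control and implementation periods.

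Recording whether NPWT was in place when the event occurred would help interpretation but is optional.

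The cost is one revised paragraph and somewhat more control-period events to record. Sample size and treatment are unchanged. The change is best made before data collection, because events that were never recorded in usual-care children may not be fully recoverable. If collection has begun, each site should be asked which reading it has used.

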**13.2 Withdrawal from project**

Participants (patients, parents/caregivers, and clinicians) may withdraw from the study at any time for any reason. Patients, parents, and caregivers will be reassured that withdrawal will not affect their routine treatment or relationship with those treating them or relationship with participating sites. Clinician participants will be reassured that withdrawal will not affect their relationship with their employers or management team. Once the decision to withdraw has been made, participants will also be given the option to have their previously collected data removed. The reidentification for removal may occur locally and the central data collection team are provided only with the study number for the participant. We will ask the participants (clinician or patient) if they are comfortable with the investigators keeping their data collected to date for research purposes, or alternatively, if they are withdrawing participation prospectively and previously collected data

**14. DISSEMINATION**

Following data analysis and write-up, the study report will be submitted to a peer-reviewed medical journal, preferably under an open access format to permit free access to the published study. During surveys and focus groups, participants can elect to receive a newsletter and or a project completion report, summarising the findings. De-identified raw data will be stored within a data repository and made available to other researchers upon reasonable request and following review of such a request by the original ethics committees. Results from this investigation will also be presented at local and international medical conferences and disseminated to relevant stakeholders and knowledge users at each of the Australian sites.

**15. SIGNIFICANCE**

Not only will this study achieve the goals of the clinical partner (such as embedding evidence-based care and improving patient outcomes), but this study will also inform policy and practice nationally on how NPWT for children with acute burns can be implemented into various contexts of burn care. Whilst significant morbidity still exists for children with burns, innovative, cost effective, and sustainable solutions are required to decrease healing time and decrease the risk of scarring. This funding application provides a practical solution to a national problem. Evidence generated will inform paediatric burn care internationally. Through rigorous implementation methodology, this project will impact and sustain the INPREP Pathway beyond the funded study. This project will be the world’s first large-scale study to evaluate the implementation of NPWT for paediatric burns. Other key project outcomes will include:

- 1. Map of Australian acute paediatric burn care models of care and co-designed INPREP Pathway to nest within it
  2. Evidence-based implementation strategies
  3. Improved patient outcomes
  4. Identification of the biological and biochemical mechanisms underpinning the effectiveness of NPWT on acute burn wounds
  5. Development and distribution of education/training resources
  6. Cost-effective implementation
  7. Standardisation (sensitive to context)
  8. Comprehensive dissemination using innovative and diverse approaches via our website, training packages, social media/podcasts, webinars to implement NPWT and achieve benefits broadly and sustainably

